### Developmental trajectories of cognitive variability

A key question that the CODEC study seeks to address is to better understand the developmental trajectories of cognitive variability, and whether the shape and speed of this development differs between children. Early results consistently suggest that within-person trial-to-trial variability is present in people across the entire lifespan, both at the behavioural and cognitive level [64]. In childhood, cognitive variability has been demonstrated in infancy [80], 18-to-35 month olds [81], preschool children [56, 82], and older children [83–85]. Longitudinal studies in childhood are sparse, but it has been suggested that children’s variability decreases across childhood from the age of 6 years to adolescence [17], potentially reflecting their relation to mean performance and myelination. Moreover, a recent study by Cubillo et al. [86] found that variability on a working memory task decreased with training over time and that this variability was a predictor of academic outcomes 6–12 months later.

Later in life, variability increases again as demonstrated in cross-sectional findings, which is in association with observed lower cognitive performance in older age [17, 87]. Longitudinally, cognitive variability increases linearly from early adulthood into late adulthood and predicts cognitive decline [88–90]. Together, these studies suggest a U-shaped pattern across the lifespan, with high variability in early life as well as old age [90–92].

### Long-term predictive value of cognitive variability

Besides investigating variability at each measurement and its development across measurements, we are also interested in the predictive value of variability for later outcomes. For instance, cognitive variability has been shown to forecast between-subject differences in important developmental outcomes such as academic achievement [86], and children’s neurodevelopmental symptoms such as ADHD and Autism Spectrum Disorder (ASD) [93–95]. This suggests that early variability could be used as a marker for the detection of later neurodevelopmental disorders, but longitudinal data are scarce. Another example of the predictive value of variability for later outcomes is based on children’s developmental changes and learning processes with regards to exploring and refining cognitive strategies. As children grow older, their strategy-related variability might diminish as the creation of novel neural connections decreases [96]. Thus, the degree of children’s exploration, their cognitive variability, and their white-matter microstructure potentially relate. This association between changes in neural and cognitive variability over time and across various cognitive domains has not been examined to date. While higher variability has been related negatively to cognitive performance [26], in tasks that require exploration, cognitive variability might actually improve performance because it allows children to try out different strategies. This behavioural variability could manifest as greater neural variability and non-overlapping neural networks during tasks. This means that in some tasks, there could be a positive relation between neural and cognitive variability.

We will test the predictive value of variability for academic achievement, cognitive growth (i.e., slopes in mean performance), neurodevelopmental disorder symptomatology (e.g., inattention, cognitive control), and additionally for cognitive performance (on all tested domains) and neural outcomes.

#### CODEC-MRI

A subset of ~200 participants will also take part in a neuroimaging arm, which consists of two MRI sessions at the Donders Institute for Brain, Cognition and Behaviour (in the first year of testing and approximately 3 years later). This enriched arm of the study, including a set of standardised questionnaires, will allow us to determine the role of brain structure and function in supporting cognitive dynamics, capture a richer picture of the psychological phenotypes associated with variability, and enables us to determine mechanistic underpinnings of variability.

### Study population

Six hundred children are recruited from schools and on an individual basis to take part in the behavioural testing. Every child who participates in the behavioural arm is invited to participate in the imaging arm (CODEC-MRI) at the Donders Institute. Based on previous experiences in similar studies, we expect approximately 1/3 of children will also enrol in the imaging arm, for a sample size of 200. Parents or caretakers of this subgroup are also asked to respond to a set of questionnaires and take part in the behavioural tasks.

In order to be eligible to participate in the behavioural arm of this study, a subject must meet all of the following criteria:Between the ages of 7 and 10 years at the moment of the first assessment.^1^The participant is able to understand the instructions of the behavioural tasks given in the Dutch language.Parents/guardians have provided written informed consent.

In order to be eligible to participate in the imaging arm of this study (CODEC-MRI), a subject must meet all of the following criteria:Between the ages of 8 and 10 years at the moment of the first MRI assessment.The participant is able to understand the instructions of the behavioural tasks given in the Dutch language.No history of neurological or psychiatric illness.No history of using psychotropic medications.No metal parts that cannot be removed, are present in or on the upper body, e.g., plates, screws, aneurysm clips, metal splinters, piercings or medical plasters (exception: dental fillings, crowns, a metal wire behind the teeth, tattoos).Body does not contain metal fragments, in particular in the eye, e.g., caused by injuries.No history of brain surgery.No active implant(s) (e.g., pacemaker, neurostimulator, insulin pump, ossicle prosthesis).Not using a medical plaster that cannot or may not be taken off.Parents/guardians have provided written informed consent.

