**Aim (3) Long-term consequences:** Our last class of predictions concerns long-term outcomes of individual differences in variability. Using latent growth curve models, we will study how variability and mean performance evolve over time, and how differences in variability are associated with faster, or slower, rates of cognitive development and the emergence of subclinical neurodevelopmental symptomatology (e.g. ADHD symptoms).*Hypothesis 3.1: Variability will decrease over developmental time. Specifically, a growth model with variability as observed scores will show a mean negative slope (less variability over time), as well as significant slope variance (individual differences in the rate of change over time). A basis model (which can capture a decelerating decrease) will outperform a linear model.**Hypothesis 3.2: Changes in variability across tasks will show distinct developmental trajectories, as variability reflects task-specific expertise. Specifically, a multivariable latent growth curve model with freely estimated slope covariances will fit better than a simpler model with these covariances fixed to unity (i.e., a unidimensional factors-of-curves model), in line with distinct developmental trajectories.**Hypothesis 3.3: Greater variability on simple tasks, and low temporal resolution (day-to-day), is associated with poorer long-term outcomes (shallower developmental slopes).**Hypothesis 3.4: Great variability on complex tasks, but only at the trial-to-trial level, is associated with better long-term outcomes (steeper slopes).**Hypothesis 3.5: Greater variability at baseline will be associated with stronger ADHD symptomatology at baseline, as well as more rapid increase in ADHD related symptomatology.*

A secondary long-term aim is to link individual differences in variability to longitudinal academic success (Cito-scores).*Hypothesis 3.6: Greater variability on simple tasks, and low temporal resolution (day-to-day), is associated with poorer long-term academic achievement (shallower developmental slopes).**Hypothesis 3.7: Great variability on complex tasks, but only at the trial-to-trial level, is associated with better long-term academic outcomes (steeper slopes).*

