## Discussion

Children’s cognitive performance fluctuates across temporal resolutions, and these fluctuations are known as within-subject cognitive variability. Cognitive variability could act as a potential early predictor of neurodevelopmental disorders [20, 21]. Despite the potential importance of cognitive variability, multiple factors including a lack of appropriate quantitative techniques and the unavailability of sufficiently rich datasets (including estimates across various tasks and temporal resolutions), cognitive variability, its underlying mechanisms and long-term implications are relatively neglected in the current literature.

The CODEC study addresses these remaining gaps by combining an accelerated longitudinal design including a behavioural ‘burst’ measurement (3 times per day, 5 days per week) and deep phenotyping, including fMRI, eye-tracking and a set of questionnaires, with advanced statistical methodologies. 600 children (age 7–12 at first measurement) are followed for up to 3 years as they undergo rapid cognitive development. Each year consists of a ‘burst’ week of experience sampling assessments of five cognitive domains (reasoning, working memory, processing speed, vocabulary, exploration), sleep quality, mood, and background noise, conducted both in classrooms and home settings. Academic outcomes and task preference are also collected once a year. A subset of 200 children of the CODEC participants take part in the deep phenotyping sessions (CODEC-MRI), once at the start of the study, in year 1, and once at the end in year 3. In addition to the cognitive battery, the deep phenotyping session consists of structural and functional MRI, eye-tracking, parental measurements (on the cognitive battery) and questionnaire-based demographic and psychosocial measures as reported by parents and children. Analysing the data through Dynamic Structural Equation Modelling, allows us to simultaneously capture variability and the multilevel structure of trials nested in sessions, days, children and classrooms. In doing so, we aim to pave the way to a better understanding of cognitive variability and its implications, providing insight into the mechanisms and consequences.

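### The ADHD and inattention associations are powered at N = 600 in the behavioural arm, but ADHD-related symptoms are described only in the imaging arm of about 200, which excludes any psychiatric or psychotropic history

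*Protocol article*

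**What the plan says.** Key hypotheses, Aim 3, states Hypothesis 3.5: "Greater variability at baseline will be associated with stronger ADHD symptomatology at baseline, as well as more rapid increase in ADHD related symptomatology". The paragraph introducing Aim 3 speaks of subclinical symptoms. It does not assign the hypothesis to an arm.

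Sample size considerations, Behavioural arm, lists variability with ADHD symptoms (r = 0.39) and inattention with variability (r = 0.24), each at 100% power. The caption of Fig. 9 bases this on the baseline sample of 600.

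The Behavioural assessment section lists what that arm collects: task performance and response times, background noise, mood and sleep sliders, a ranking of the tasks, academic results and basic demographics. It lists no symptom scale. The SDQ (with its hyperactivity subscale) and BRIEF-2 appear only under Imaging assessment, where accompanying parents who agree complete them at each session. Recruitment and enrolment makes parental participation optional and asks for fresh consent for the second session.

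Study population sets stricter criteria for imaging than for behavioural testing. They include "No history of neurological or psychiatric illness", no psychotropic medication history, and "Between the ages of 8 and 10 years at the moment of the first MRI assessment". On numbers it says "Every child who participates in the behavioural arm is invited to participate in the imaging arm (CODEC-MRI) at the Donders Institute" and "we expect approximately 1/3 of children will also enrol in the imaging arm, for a sample size of 200".

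**The concern.** The sample that carries the power claim and the sample that carries the outcome are different. A reader of the sample size section would conclude that the ADHD and inattention associations are tested in 600 children with power at ceiling. On the measures described, 400 of those children have no symptom score.

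The children who do have scores are also selected in a way related to the outcome. Those with a psychiatric diagnosis or medication history, who are likely to sit at the upper end of ADHD symptoms, can enter the arm without symptom data but not the arm with it. Restricting the range of one variable lowers its correlation with the other and limits whom the result describes. Neither the power section nor the Discussion mentions this.

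At stake are the power figure for Hypothesis 3.5 and the population to which its answer applies.

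**Working it through.** **Inputs from the article.** Behavioural N = 600; imaging N = 200; r = 0.39 (ADHD), 0.24 (inattention), 0.34 (expected imaging effect) and 0.2 (smallest imaging effect with a power claim). Alpha and sidedness are not given; two-sided 0.05 is assumed.

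**Formula.** Power = Φ(atanh(r)·√(N − 3) − 1.96).

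**1. The article's own figures.**
- N = 600, r = 0.39 and r = 0.24: 100% each, as stated.
- Imaging N: 600 × 1/3 = 200, as stated.
- N = 200, r = 0.2: 0.2027 × 14.04 − 1.96 = 0.886, so 81.2%. For r = 0.3: 99.1%. Both agree with the stated >80% and >99%.

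**2. Power at the N that has symptom data.**
- N = 200, r = 0.39: 99.99%.
- N = 200, r = 0.24: 0.2448 × 14.04 − 1.96 = 1.476, so 93%.

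**3. Range restriction.** The article gives no rate of psychiatric or psychotropic history. As an assumption, let the exclusion remove the top 5% or 10% of a normal symptom score. The SD ratio u is then 0.90 or 0.84, and r′ = r·u / √(1 − r² + r²u²). Simulation of a truncated bivariate normal gives the same values to two decimals.

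| Unrestricted r | Removed | r′ | Power, N = 200 | Power, N = 150 |
|---|---|---|---|---|
| 0.39 | 5% | 0.36 | 99.9% | 99.5% |
| 0.39 | 10% | 0.34 | 99.8% | 98.9% |
| 0.24 | 5% | 0.22 | 87% | 76% |
| 0.24 | 10% | 0.20 | 83% | 71% |

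N = 150 only illustrates fewer parents taking part; the article gives no such figure. The article also gives no separate effect size for symptom change, so power for that half of Hypothesis 3.5 cannot be derived. Its N is limited to families with questionnaires at both imaging sessions.

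**4. Slack in the 200.** Solving for 80% power at r = 0.2: N = ((1.960 + 0.842)/0.2027)² + 3, which rounds up to 194. A shortfall of more than six children takes this claim below 80%. If the one-third applied only to eligible children and 95% or 85% of the 600 were eligible (assumption), N would be 600 × 0.95/3 = 190 or 600 × 0.85/3 = 170, with power of 79% or 75%. At r = 0.34 only 66 children are needed.

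**The case against.** The strongest defence is that Hypothesis 3.5 fits its sample. Aim 3 concerns emerging subclinical symptoms, and children without a psychiatric history can show and develop them. At r = 0.39, the value quoted for ADHD symptoms, power is still about 94% with the top 15% of scores removed and only 113 children. The r = 0.24 figure concerns inattention, and at N = 200 it stays above 80% in both scenarios tabulated above. Exclusion is also by history and not by score, so if the two match imperfectly, removing the same share of children attenuates less than shown. All of this stands, and it limits the point to a misstated sample and an unacknowledged restriction.

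A reader might infer more, in four ways that the documents do not support:

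- **That 7-year-olds cannot enter imaging.** Behavioural entry is "Between the ages of 7 and 10 years at the moment of the first assessment", while the imaging limit applies at the first MRI, which falls in the first year of testing. A child enrolled at 7 can qualify after turning 8.
- **That 200 is unattainable.** The one-third is an enrolment rate drawn from similar studies and may already be net of ineligible children. Reducing it again could count the same loss twice. Only its basis is unstated.
- **That inviting every child contradicts the criteria.** Eligibility limits who enrols, not who is approached.
- **That the Discussion overclaims.** The sentence "Cognitive variability could act as a potential early predictor of neurodevelopmental disorders" is cited background, not a conclusion to be drawn from Hypothesis 3.5.

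**Conclusion.** The point holds as a mismatch between the stated power and the described data. The 100% power at N = 600 for the ADHD and inattention associations does not belong to a sample the described design delivers. Symptom data exist for at most about 200 children, fewer if parents decline, and fewer again for change.

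The size is modest. At r = 0.24, power falls from 100% to about 93% at N = 200, and to about 83-87% with the assumed 5-10% truncation. At r = 0.39 the baseline test remains well powered. These figures rest on two-sided alpha 0.05, normal scores, and exclusion acting as a cut at the top of the symptom scale.

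The history exclusion does not invalidate Hypothesis 3.5. It attenuates the association and confines the inference to children without a psychiatric or psychotropic history. Separately, the imaging claim at r = 0.2 has almost no slack (194 of 200 needed), so the basis of the one-third should be stated. The arm's expected effect of r = 0.34 is not at risk.

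**What to change.** Changes to the text, at no cost beyond redrafting:

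1. Name the imaging arm, and within it the children with parent questionnaires, as the analysis sample for Hypothesis 3.5. Give the expected N separately for baseline and for change.
2. Move the ADHD and inattention power statements out of the N = 600 paragraph. Restate them at N of 200 or less, with the alpha, the sidedness and an explicit range-restriction assumption.
3. Limit the conclusion of Hypothesis 3.5 to children without a psychiatric or psychotropic history.
4. State whether the one-third uptake is net of the imaging criteria. If it is not, derive the imaging N from the eligible number and give the uptake needed to reach 200.

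Optional: if the sponsor accepts the added parent burden, collect a short parent symptom scale, such as the five-item SDQ hyperactivity subscale, in the whole behavioural cohort and test Hypothesis 3.5 there. This would match the sample to the stated power and avoid the history exclusion. It is new data collection, needing an ethics amendment and extra parent time, and the article places its standardised questionnaires in the imaging arm by design. The text changes suffice without it.

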### Recruitment and enrolment

There are two initial recruitment routes. Our core recruitment strategy will be through schools in the Netherlands, mainly in and around Nijmegen. The other recruitment is at the individual (non-school based) level, discussed later.

During school recruitment, schools are contacted and receive information on the study. This information is in the form of an email, an information sheet, and a link to the CODEC study website [97] including informational videos of the aims and procedure of our study. Schools can be contacted by phone to follow-up several days after receiving the information by email. Parents/guardians receive an information sheet and consent form from the participating school and are asked to sign and return the informed consent when giving consent for their child to take part in the study.

Individuals willing to take part in the study, but whose school/classroom does not or cannot participate, can be recruited on an individual basis. The parents/guardians who have expressed interest in participating receive a dedicated informed consent and information sheet either in person, by post or email, depending on their preference. Parents or guardians of participants are asked to give, or decline, consent for 1) participation in the behavioural study, and additional consent 2) to be contacted to receive more information about the imaging study, 3) for the researcher to obtain Cito scores (or equivalent academic results) through the school (only for those children recruited in classrooms), and 4) to be contacted to receive more information for other follow-up studies. Agreeing to 1 is possible without agreeing to 2, 3 and/or 4. For participants consenting to be contacted for the imaging study or follow-up studies, the preferred means of communication (phone or email) is requested, and the relevant information provided. Parents are contacted through their preferred means of communication (either through post, email or in person) and receive the information sheet and informed consent for the imaging part (if agreed upon). Parents or guardians give consent on the ‘imaging’ informed consent form to have their child take part in the imaging study (CODEC-MRI). An additional informed consent form asks parents/guardians to perform the cognitive battery tasks, identical to the tasks performed by the child in the behavioural study and/or to respond to a set of questionnaires on their child and their environment. Parental participation is not necessary for the child to enrol in CODEC-MRI. A new consent form needs to be signed for the child to take part in the second MRI scan and for the parents/guardians to take part in the second accompanied behavioural tasks and questionnaires. 

### Study procedures and assessments

#### Behavioural procedure – school recruitment

Initial ‘burst’ week - The CODEC team organises an initial visit to the schools with the relevant teachers and hands out tablets to the children. All children perform the same tasks, but no data is collected for children for whom consent was not given. Children perform the tasks in the classroom, independently but in a group setting, for 2–3 times a day for the duration of a week using the same tablet, supported by teachers in the classroom. The precise timing of the measurement occasions is determined in collaboration with the teacher, to accommodate the school’s schedule, and thus will vary between classrooms. The first testing session will be assisted by a member(s) of the CODEC team to ensure that all task demands are clear, and any logistical (e.g., login) problems can be addressed immediately. Children have the opportunity to ask questions, and tick a box prior to starting the first testing session indicating that they have understood all instructions. In each testing session, three of the five tasks (selected pseudorandomly) are played by the child for the duration of 5 min (15 min in total) to make sure that the session remains sufficiently short and exciting for the children.

Follow-up measurement occasions - Throughout each year of testing, up to two additional testing occasions can be planned in agreement with the teachers. On these occasions, the procedure is identical, but all five cognitive tasks are performed once in a single session. Two follow-up ‘burst’ weeks take place after approximately one (in the second year of the study) and 2 years (in the final year of the study), for which the procedure is identical to the initial ‘burst’ week.

#### Behavioural procedure – individual recruitment

The procedure for individual participants is similar to the participation through schools, but testing is done in a home setting. Participants at home use an individual login-code on a personal tablet or a tablet provided by us to the parent. The parent and child are provided with all necessary instructions, guidelines and information. The first testing session may be accompanied by a CODEC team member if preferred by the parent(s) or participants. Up to two yearly, shorter additional testing occasions are possible in agreement with the parents, identical to the additional testing occasions in the school recruitment, and a yearly ‘burst’ week follow-up is organised with the parents in the same way as the initial testing session.

